### Blinding

Given the nature of the intervention, it is not possible to blind participants, HCP or researchers accessing outcomes to the intervention, as outcomes are self-reported.

### Standard HIV care

Clinics randomised to the control arm will continue to provide standard HIV care as the comparator throughout the cRCT. The standard HIV care consists of PLWHA attending their clinic appointments for either repeat prescription or for referrals to ART adherence support, nutrition support, CD4 count/viral load testing and for specific problem(s) as described by appointment note. These clinic appointments will be made to align with the 3 monthly follow-ups in the ExtraCECI arm.

### Intervention (ExtraCECI)

The ExtraCECI as described above will be targeted at both cluster and individual participant level. The difference between standard HIV care and ExtraCECI is that, while standard HIV care focuses mainly on the management of physical symptoms and ART services, ExtraCECI focuses on the holistic assessment and management of the physical, psychological, social and spiritual well-being of PLWHA in addition to ART services.

#### At cluster level

HCP will receive five sessions of intervention training delivered by [name] supported by designated study team members at agreed times using a hybrid approach (virtual and face-to-face sessions) with PowerPoint presentations and role plays using sample healthcare scenarios for practice sessions. HCP will also receive regular mentorship support after each intervention delivery including monitoring of their stress and coping levels using Occupational Stress Scale. On completion of ExtraCECI training, there will be an embedding period where HCP will continue to practice the intervention at site for approximately 4 weeks, before intervention sessions will be delivered to all recruited PLWHA based on their respective appointments.

#### At the individual participant level

At their first intervention appointment, the researcher/HCP will provide the participant with a patient education leaflet focused on ways to support/empower them for their clinical consultation, for example, how to have a meaningful conversation about their symptoms and concerns with the HCP for collaborative care planning. HCP will discuss symptoms and concerns, collaboratively plan care based on identified needs using a structured client holistic assessment form and care plans to set short/long-term goals, prioritising needs and care goals. Optimal management approach will be used and action plans individualised to achieve small realistic goals by next appointment. Postcare assessments will happen at the clinic where PLWHA will have a discussion with the researcher for care outcome assessment.

### Primary and secondary outcomes and measures

All outcomes will be assessed by designated research assistants at baseline (T0), and after each scheduled appointment: the first postrandomisation appointment (T1) and at 3, 6, 9 and 12 months thereafter (T2, T3, T4 and T5, respectively). The primary outcome is self-reported QoL measured at the individual level using MOS-HIV^43^ total score at 12-month time point. The 35-items address the domains of role function, pain, physical functioning, cognitive functioning, social functioning, general health perception, mental health, distress and vitality. The secondary outcomes will include the MOS-HIV domain scores and total score at other timepoints and positive outcomes HIV PROM,^24 44^ a 23-item patient-centred PROM that reflects the range of outcomes relevant for PLWHA to drive and evaluate care. Picker Patient Experience^45^ is an 18-item self-reported measure, which measures patient experience along the domains of communication; emotions; short-term outcomes; barriers and relations with HCP. Consultation and Relational Empathy^46^ measure, a 10-item person-centred process questionnaire that measures the amount of empathy that a patient feels they have received during a consultation. Table 2 presents the schedule for data collection for outcome measures.

**Table 2 T2:** Schedule for data collection

Data	Time point collected for both intervention and control							2 months post-trial
	Baseline	Time 1	Time 2	Time 3	Time 4	Time 5	Trial ends	
Eligibility data	✓							
Consent and contact details	✓							
Demographic and HIV history	✓							
Medical outcome study—HIV (MOS-HIV) for QoL	✓	✓	✓	✓	✓	✓		
Positive outcomes: HIV PROM—person-centredness	✓	✓	✓	✓	✓	✓		
CARE measure—person-centred process	✓	✓	✓	✓	✓	✓		
Picker Patient Experience Questionnaire (PPE-15)	✓	✓	✓	✓	✓	✓		
ExtraCECI related cost data	✓	✓	✓	✓	✓	✓		
Qualitative interviews								✓
Adverse event reporting	Ongoing							
Process evaluation	Ongoing							
Economic evaluation	Ongoing							

ExtraCECI -, Extra Community-based Enhanced Care Intervention.

### Participant compliance, loss to follow-up and withdrawal

No participant will be withdrawn from the trial based solely on non-compliance to the intervention. Participants may withdraw from the study at any time without influencing their future care.

A withdrawal form will be completed when a PLWHA does not wish to continue participating in the intervention and or trial-related activities including follow-up assessments. The withdrawal forms will be completed by research assistants/HCP, and all withdrawal data will be uploaded to Qualtrics, hosted by the York Trials Unit. We will contact HCP to request new contact details of any participant for whom we have lost contact.

### 
Adverse events

The ExtraCECI study is a behavioural intervention trial, with no medicinal product being used and thus, no medical or physical health adverse events (AEs) are expected. However, there is a low risk that conversations around psychosocial well-being could trigger distressing emotions and thoughts, which could trigger emotional breakdown. As such, researchers will be vigilant in looking out for the impact of the study on the well-being and psychological safety of study participants. For the purposes of the ExtraCECI intervention trial, AEs are defined as any untoward medical occurrence (ie, any unfavourable and unintended sign, symptom or disease), experienced by a trial participant, which is temporally associated with trial treatment (intervention or control). AEs, which might be expected, include potential general discomfort associated with responding to questionnaires, social, economic and psychological impacts. AEs which would not require reporting include medical conditions such as stroke, heart attack, accidents, infections and all other conditions requiring emergency treatment or admission for general medical services.

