## Methods and analysis

### Setting

This study will be conducted in community HIV clinics within the Greater Accra Region (GAR) of Ghana. The region has both urban and rural communities with a mixture of different socioeconomic, cultural and educational backgrounds. Of the 346,120 PLWHA in Ghana, about 76,730 PLWHA are in the GAR,^35^ with approximately 94 ART clinics and 506 HIV testing facilities. Eligible clinics provide similar HIV care services including provision of ART, care for key populations (men who have sex with men (MSM), sex workers and drug users), ART adherence, counselling, psychosocial and spiritual care.

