#### Refining CECI to ‘ExtraCECI’

The CECI components include: (1) a training programme on person-centred communication, (2) holistic assessment of PLWHA’s symptoms and concerns in the domains of physical, psychological, social, and spiritual well-being using a structured tool, (3) a care plan to capture holistic needs to facilitate collaborative care planning and delivery, (4) regular support/mentorship for HCP with fidelity monitoring.

‘Extra’ components of: (1) empowering PLWHA on how to engage, participate and contribute to their care decisions; and (2) working with HCP and Models of Hope to use telehealth (text messaging for information sharing and voice calls for follow-up, assessment and enabling feedback in the communication process) for care delivery is being added to CECI as ‘extra’ components. These extra components of CECI will rely on collaborative discussion of PLWHA’s symptoms and concerns with the HCP to inform holistic care planning and delivery. Consideration has been given to these additional components, as both HCP and PLWHA have identified the need for PLWHA to be empowered to be able on to engage, participate in care consultations and contribute to care decisions.^34^ Working with HCP and Models of Hope to use telehealth to deliver CECI gives PLWHA more options to access care through telecommunication.

The process of refinement will include:

CECI Theory of Change (ToC) workshop with stakeholders including our public and PLWHA group members, where CECI will be presented with the mechanisms of action identified during the feasibility cRCT.The areas of refinement as identified as empowering PLWHA on how to engage, participate and contribute to their care decisions will be discussed with stakeholders for their views and input.Additionally, the ToC workshop will explore how to work with HCP and Models of Hope to use mobile phones^36^ to deliver CECI, since mobile phones (eHealth) have shown to be effective in delivering interventions to PLWHA in sub-Saharan Africa.^37^Share samples of the holistic assessment and care planning tools for CECI with stakeholders for review and input.

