### Contamination

Using clusters as a unit of randomisation and maintaining a 3 km travel distance between clinics should minimise the risk of contamination. However, there is a theoretical possibility of some contamination if PLWHA in the ExtraCECI arm was to meet with PLWHA in the standard HIV care arm and then divulge information about intervention components. To minimise the possibility of any form of contamination, participants in both clusters will be asked if they visited any health facility since the last appointment. We will request those in the ExtraCECI (intervention group) to refrain from sharing study-related information and materials during the study. We will also ask those in the standard HIV care arm if they had any contact with any participant from the ExtraCECI arm.

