## Ethics and dissemination

### Research ethics approval

The trial protocol was approved by the ENU School of Health and Social Care Research Integrity Committee (REF: SHSC3681836) and the Ghana Health Service Ethics Review Committee (GHS-ERC:010/07/24). The trial will be conducted according to the approved study protocol and following GCP guidelines and all study participants will sign the consent form (see online supplemental appendix 1) prior to participation. Any substantial deviations from the protocol will be sent to the regulatory authorities for prior review and approval. Appropriate protocol is in place to support any psychological distress experienced by participants including a distress protocol developed to guide researchers in the support process and possible onward referral for further management. The assessment of the trial AE will be conducted by the delegated clinical psychologist who becomes aware of the event and supported by HCP.

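### AE counts by arm are at risk of unequal detection: researcher vigilance is the only method described, and ExtraCECI alone adds contacts in which distress can surface

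*Protocol article*

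**What the plan says.** **How AEs are found.** The Adverse events section names a low risk that talking about psychosocial well-being could cause distress. It draws from this that "researchers will be vigilant in looking out for the impact of the study on the well-being and psychological safety of study participants". The article describes no other way of finding AEs. Table 2 lists AE reporting as ongoing, under a heading that covers both arms, and the AE definition also covers both arms.

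**Who assesses them.** Under Research ethics approval: "The assessment of the trial AE will be conducted by the delegated clinical psychologist who becomes aware of the event and supported by HCP". The section on the joint committee says that a smaller DMC monitors AEs, and that the committee reviews all serious AEs and those thought to be treatment-related and unexpected.

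**Blinding.** The Blinding section says that "it is not possible to blind participants, HCP or researchers accessing outcomes to the intervention, as outcomes are self-reported".

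**What differs between the arms.** Under Intervention (ExtraCECI), "standard HIV care focuses mainly on the management of physical symptoms and ART services", whereas "ExtraCECI focuses on the holistic assessment and management of the physical, psychological, social and spiritual well-being of PLWHA in addition to ART services". The individual-level description adds a structured assessment form and care plans. The refinement section adds telehealth, including "voice calls for follow-up, assessment and enabling feedback in the communication process". The cluster-level description adds mentorship of HCP after each delivery.

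**What is the same in both arms.** Control appointments are aligned with the 3-monthly follow-ups. Research assistants assess everyone at T0 to T5, and the MOS-HIV covers mental health and distress. All eligible clinics are said to offer "ART adherence, counselling, psychosocial and spiritual care".

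**The concern.** If AEs come to notice only when somebody happens to see or hear of them, the count depends on how many occasions there are for that and on who is looking. ExtraCECI adds such occasions. The vigilance is also motivated by the kind of conversation that is central to ExtraCECI, and the people being vigilant know the allocation. The same distress could therefore be recorded more often under ExtraCECI than under standard care.

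At stake is the reading of AE counts by arm. An excess under ExtraCECI could be a true effect of the conversations, which the protocol itself allows for, or an effect of closer observation. Equal counts could hide a difference in the same way. Neither the committee nor a later reader could tell these apart.

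**Working it through.** **No figure to reproduce.** The article gives no AE rate, no detection probability and no AE analysis. The sample size was set for the MOS-HIV and does not bear on this point, except that 650 participants at 1:1 allocation make about 325 per arm.

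**Step 1: how detection enters the count.** Recorded risk = true risk × detection probability. So

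recorded risk ratio = true risk ratio × (detection in ExtraCECI ÷ detection in control).

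With equal true risk, the recorded ratio is the detection ratio alone, whatever the true risk is.

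**Step 2: illustration.** Every value here is an assumption except 325. Take a true risk of 5% in both arms: 325 × 0.05 = 16.25 participants with an event per arm.

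| Detection, ExtraCECI v control | Recorded, ExtraCECI v control | Recorded risk ratio |
|---|---|---|
| 80% v 80% | 13.0 v 13.0 | 1.0 |
| 80% v 60% | 13.0 v 9.8 | 1.33 |
| 90% v 50% | 14.6 v 8.1 | 1.8 |
| 80% v 40% | 13.0 v 6.5 | 2.0 |
| 90% v 30% | 14.6 v 4.9 | 3.0 |

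The ratios are the same for true risks of 2% and 10%; only the counts change.

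**Step 3: how far equal research visits limit this.** Suppose that research visits detect a share d of events in both arms, and that the extra ExtraCECI contacts bring out a share e of the events that those visits miss. Detection is then d in control and d + (1 − d)e in ExtraCECI, so the ratio is

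1 + (1 − d)e ÷ d, which is at most 1 ÷ d.

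- The row 80% v 60% corresponds to d = 0.6 and e = (0.8 − 0.6) ÷ (1 − 0.6) = 0.5.
- If research visits alone detected 80%, the ratio could not exceed 1 ÷ 0.8 = 1.25.
- If they detected 40%, it could reach 1 ÷ 0.4 = 2.5.

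So the higher and more uniform the detection at research visits, the less the extra contacts can distort the count. This step assumes that d is the same in both arms. A common fixed question supports that assumption better than unblinded vigilance does.

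**Step 4: does the article already provide a common prompt?** The nearest is in the Contamination section: "participants in both clusters will be asked if they visited any health facility since the last appointment". It serves to monitor contamination, and nothing links the answer to AE reporting. The MOS-HIV distress items are collected equally, but nothing says that a score leads to an AE report.

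**The case against.** The strongest reply is that the quoted sentence concerns participant welfare in a condensed article. A standard AE form and prompts may be in the full protocol, and a distress protocol is mentioned but not shown. This stands as a limit: the article does not show that no prompt exists. If an identical AE question is already asked in both arms, confirming that would settle most of the point.

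Second, the vigilance is that of the researchers, and their scheduled contact is the same in both arms. The extra contact is with HCP and Models of Hope, and the article does not say that it feeds the AE count. Psychosocial care exists in control clinics too, so the contrast is one of degree. The MOS-HIV also measures distress systematically, apart from AE reports. All of this stands and reduces the likely size, but equal visits without a described common question do not ensure equal detection.

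Third, the illustrations only divide assumed detection rates. Even 15 against 8 recorded events would give z of about 1.5 before allowing for clustering, so it would not show a clear difference between arms. That is correct. The illustrations show the mechanism and do not estimate its size.

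A reader might also infer three stronger points that the document does not support:

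- **That the trial's comparison of harms is biased.** The article states no between-arm analysis of harms; the analysis section covers the MOS-HIV and the continuous secondary outcomes.
- **That HCP who delivered a session judge whether an event is related to it.** The article gives the assessment to a clinical psychologist, and says neither that the supporting HCP judge relatedness nor that they delivered the session.
- **That psychological harm is the only expected AE.** The article also lists discomfort from questionnaires and social and economic impacts.

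**Conclusion.** The concern holds as a risk of unequal detection, not as a demonstrated bias. It rests on three things that the article states: vigilance is the only detection method described, nobody involved is blinded, and ExtraCECI alone adds structured holistic assessment and follow-up calls. It applies to AE counts by arm that the committee sees or that are reported later.

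The size cannot be estimated from the document. Under the assumed detection rates and equal true risk, the recorded risk ratio ranges from 1.0 to 3.0; the equal research visits and MOS-HIV distress items make the upper end less likely. The probable direction is more recorded events under ExtraCECI, but part of any excess could be real. The primary MOS-HIV analysis is not affected. The change is a cheap improvement.

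**What to change.** 1. At T1 to T5, the research assistant asks every participant in both arms the same short fixed question on distress and on social or economic harm since the last assessment. Baseline is left out, because no earlier assessment exists to count from.
2. For each AE report, record the source: research visit, HCP session, call or mentorship.
3. Base any summary of AEs by arm on the answers to the fixed question. List events found only through ExtraCECI contacts separately, so that they remain visible to the committee without entering the comparison.

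Health-facility visits should stay out of the harm summary. The Adverse events section exempts conditions that need emergency treatment or admission from reporting, so counting such visits as harms would conflict with it.

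The cost is about a minute more per visit, at visits already scheduled, plus a source field on the AE record and a few lines of wording. Design, sample size and care are unchanged. The question gives both arms the same opportunity to report; it cannot remove the effect of participants and research assistants knowing the allocation.

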### Joint trial steering committee and data monitoring committee

Due to the low risk profile of the ExtraCECI intervention, a combined steering and data monitoring committee (DMC) will be sought. Therefore, a trial steering committee (TSC) will be convened to provide overall supervision of the trial, ensuring its conduct is in accordance with the protocol and relevant regulations for trial safety. Within the TSC, a smaller DMC will monitor adverse and serious AEs related and unrelated to the trial. The committee will consist of an independent chair and at least two other independent members including a statistician and two context and subject expert, and one PPI, along with the PI, the trial manager and representative from the clinical trials unit. Other study collaborators may also attend the meeting at the discretion of the Chair. The TSC/DMC will meet two times a year to discuss progress of the trial, or more often as appropriate. The role of this committee will also include the review of all serious AEs, and the AEs which are thought to be treatment-related and unexpected.

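### General medical emergencies and admissions are exempt from adverse event reporting with no exception for serious events, yet the DMC is charged with reviewing all serious AEs, related or not

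*Protocol article*

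**What the plan says.** Three statements in the protocol article bear on this.

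- **Definition (Adverse events).** "AEs are defined as any untoward medical occurrence (ie, any unfavourable and unintended sign, symptom or disease"), provided it is experienced by a participant and temporally associated with intervention or control. Causality is not part of the definition.
- **Exemption (same section).** "AEs which would not require reporting include medical conditions such as stroke, heart attack, accidents, infections and all other conditions requiring emergency treatment or admission"; the last clause reads in full "all other conditions requiring emergency treatment or admission for general medical services".
- **Committee remit (Joint trial steering committee and data monitoring committee).** "Within the TSC, a smaller DMC will monitor adverse and serious AEs related and unrelated to the trial". The section ends by adding that "The role of this committee will also include the review of all serious AEs", together with those AEs considered treatment-related and unexpected.

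The Contamination section is also relevant: "participants in both clusters will be asked if they visited any health facility since the last appointment".

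**The concern.** The conditions taken out of reporting are typical unrelated serious events in an adult outpatient population. They are also the events that the committee section says will be seen. The sites and the committee would therefore work to different rules across 26 clinics.

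What is at stake is whether the promised oversight can be carried out. The article's own rationale makes medical events a fair question. The Introduction links psychological symptoms to poorer adherence and viral rebound, and links good psychosocial care to better clinical outcomes and retention. A difference between arms in serious events, in either direction, is something a monitoring committee might reasonably want to see.

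**Working it through.** No arithmetic applies, and the article states no figure to reproduce. The check sets the statements against each other.

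**Step 1: is an unrelated stroke or admission an AE?** Yes. The definition asks only for an untoward occurrence temporally associated with either arm.

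**Step 2: must it be reported?** No. Stroke, heart attack, accidents and infections are exempt by name. A catch-all then covers other conditions needing emergency treatment or admission, with the qualifier about general medical services. Nothing is kept back for serious events.

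**Step 3: is it within the committee's remit?** Yes, if it is serious. The remit names unrelated events expressly. In the closing sentence of that section, the words about treatment-related and unexpected events describe a second group of AEs; they do not limit the review of serious ones.

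**Step 4: compare by type of event.** The article does not define a serious AE. The table assumes that a death, or an event that leads to admission, counts as serious.

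| Event | Duty to report | Within DMC remit |
|---|---|---|
| Stroke or heart attack, admitted | None (exempt by name) | Yes |
| Accident or infection, admitted to general medical care | None (exempt) | Yes |
| Psychiatric admission | Not clearly exempt | Yes |
| Death | Not named in the exemption; unclear if the cause is an exempt condition | Yes |

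The first two rows contradict each other. The last two are uncertain.

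**Step 5: is there another required route?**

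- Table 2 lists AE reporting as ongoing, but that reporting is what the exemption limits.
- Research ethics approval gives AE assessment to a delegated clinical psychologist supported by HCP. It describes no separate path for serious medical events.
- The health-facility question in the Contamination section is asked in both arms, but to monitor contamination. Nothing links the answers to safety reporting.

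None of these supplies the route.

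**Step 6: could voluntary reports fill the gap?** Not reliably. The Blinding section says that participants, HCP and researchers are unblinded. Under the cluster-level description of the intervention, HCP in that arm receive mentorship after each delivery. The chance that an optional report is made could therefore differ by arm even if true incidence does not.

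**The case against.** The strongest counter-argument is that a low-risk behavioural trial may properly limit AE reporting to what the intervention could plausibly cause. The article expects no medical AEs, names emotional distress as the foreseeable harm and provides a distress protocol. The committee section could then be read as covering only those serious AEs that are reportable, whether related or not. This would be a defensible policy, but it is not what the committee section says: it refers to all serious AEs without that limit.

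A second argument is that a journal article condenses a fuller protocol, which may define serious AEs and set out reporting routes. That is a fair caution about consequences in practice. A definition alone, however, would not reconcile an exemption that covers emergency treatment and admission with a duty to review every serious event.

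Several stronger readings are tempting and are not supported:

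- A reader might infer that every hospital admission is exempt. The qualifier about general medical services leaves psychiatric and similar admissions possibly reportable.
- A reader might infer that the committee would never see a serious medical event. The text removes a duty to report; it does not forbid reporting.
- A reader might infer that deaths are exempt. They are not named.
- A reader might infer that telehealth replaces clinic review and so raises risk. The section on refining CECI presents it as an added option for access, and clinic appointments continue.
- A reader might want a count of unreported events. The article gives no rate, and participants are selected to be clinically well, so multiplying 650 by an assumed rate would only restate the assumption.

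It also stands that safety is not a listed objective and that the article promises no conclusion of no harm.

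**Conclusion.** The contradiction is in the current text and should be corrected. As written, the committee has no required route to most unrelated serious medical events, although its remit covers all of them, and optional reports from unblinded sites could differ by arm. This rests on two assumptions: that conditions such as stroke, heart attack and those needing admission would count as serious, and that no document outside the article restores reporting for them.

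No event count can be derived from the documents. The primary outcome, sample size, randomisation and effectiveness analysis are untouched. The point still matters because it concerns participant safety, and events not recorded as the trial proceeds may be hard to recover later.

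**What to change.** Reconcile the Adverse events section with the committee section. There are two coherent ways, and the choice is for the sponsor and the committee.

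1. **Keep the stated remit.** Limit the reporting exemption to non-serious general medical events. Record serious events, including deaths and admissions, in both arms at the scheduled visits regardless of relatedness. The health-facility question already asked in both arms could be extended for this. A death will not surface through a question put to the participant, so it needs a report from the clinic. Give the DMC counts by arm, and keep expedited review for related and unexpected events.
2. **Narrow the remit.** Reword the committee section so that it no longer promises review of all serious AEs, related and unrelated, and state that the trial cannot compare serious medical events between arms.

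The first option needs a short amendment to the protocol and the committee's terms of reference, and a few added fields on the case report form (such as date, reason, seriousness and outcome). Its downside is modest extra reporting by sites. The second costs only wording, but gives up the comparison.
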